#### **Data and Safety Monitoring Board**

- **[name] (*Chair*)** | Kingston General Hospital, Queens University, Kingston, ON, Canada
- **[name] [name]** | MaineHealth Maine Medical Center Portland, Tufts University School of Medicine, Portland, ME, United States
- **Prof [name]** | CHUS - Hôpital Fleurimont, Université de Sherbrooke, Sherbrooke, QC, Canada

***Supplemental table 1:*** Morphine milligram equivalent conversions.

| Opioid | Administrative Route | MME Conversion Factor |
|---------------|-----------------------------|------------------------------|
| Codeine       | Oral                        | 0·15                         |
| Fentanyl      | Intravenous                 | 0·2                          |
| Hydromorphone | Intramuscular               | 15                           |
| Hydromorphone | Intravenous                 | 15                           |
| Hydromorphone | Oral                        | 4                            |
| Hydromorphone | Subcutaneous                | 15                           |
| Meperidine    | Intravenous                 | 0·4                          |
| Morphine      | Intravenous                 | 3                            |
| Morphine      | Oral                        | 1                            |
| Morphine      | Subcutaneous                | 3                            |
| Oxycodone     | Oral                        | 1·5                          |
| Sufentanil    | Intravenous                 | 2                            |
| Tramadol      | Oral                        | 0·1                          |

MME=morphine milligram equivalent.

[figure not shown]

# Clinical Trial Protocol

## 1. Protocol Synopsis

|                       |                                                                                                                                                                                                                                                                                                                                                                                                                                                                                                                                                                                                                                                                                                                                                                                                                                                                                                                                                                                                                                                                                                                                                                                                                                                                                                                                                                                                                                                                                                                                                                                                                                                                                                                                                                                                                                                                     |
|-----------------------|---------------------------------------------------------------------------------------------------------------------------------------------------------------------------------------------------------------------------------------------------------------------------------------------------------------------------------------------------------------------------------------------------------------------------------------------------------------------------------------------------------------------------------------------------------------------------------------------------------------------------------------------------------------------------------------------------------------------------------------------------------------------------------------------------------------------------------------------------------------------------------------------------------------------------------------------------------------------------------------------------------------------------------------------------------------------------------------------------------------------------------------------------------------------------------------------------------------------------------------------------------------------------------------------------------------------------------------------------------------------------------------------------------------------------------------------------------------------------------------------------------------------------------------------------------------------------------------------------------------------------------------------------------------------------------------------------------------------------------------------------------------------------------------------------------------------------------------------------------------------|
| Full Title            | Efficacy of Superficial Parasternal Intercostal Plane Block on Postoperative Pain Control in Patients Undergoing Cardiac Surgery with Median Sternotomy                                                                                                                                                                                                                                                                                                                                                                                                                                                                                                                                                                                                                                                                                                                                                                                                                                                                                                                                                                                                                                                                                                                                                                                                                                                                                                                                                                                                                                                                                                                                                                                                                                                                                                             |
| Short Title           | EPOCH CardioLink-10 RCT                                                                                                                                                                                                                                                                                                                                                                                                                                                                                                                                                                                                                                                                                                                                                                                                                                                                                                                                                                                                                                                                                                                                                                                                                                                                                                                                                                                                                                                                                                                                                                                                                                                                                                                                                                                                                                             |
| Funding               | CardioLink Clinical Trial Platform                                                                                                                                                                                                                                                                                                                                                                                                                                                                                                                                                                                                                                                                                                                                                                                                                                                                                                                                                                                                                                                                                                                                                                                                                                                                                                                                                                                                                                                                                                                                                                                                                                                                                                                                                                                                                                  |
| Study Population      | Adult patients undergoing cardiac surgery via median sternotomy                                                                                                                                                                                                                                                                                                                                                                                                                                                                                                                                                                                                                                                                                                                                                                                                                                                                                                                                                                                                                                                                                                                                                                                                                                                                                                                                                                                                                                                                                                                                                                                                                                                                                                                                                                                                     |
| Study Design          | Randomized, double-blinded, parallel-group, multicentre trial of superficial parasternal intercostal plane block with ropivacaine via ultrasound-guided catheter placement versus sham block with saline in cardiac surgical patients undergoing median sternotomy.                                                                                                                                                                                                                                                                                                                                                                                                                                                                                                                                                                                                                                                                                                                                                                                                                                                                                                                                                                                                                                                                                                                                                                                                                                                                                                                                                                                                                                                                                                                                                                                                 |
| Sample Size           | 340 patients                                                                                                                                                                                                                                                                                                                                                                                                                                                                                                                                                                                                                                                                                                                                                                                                                                                                                                                                                                                                                                                                                                                                                                                                                                                                                                                                                                                                                                                                                                                                                                                                                                                                                                                                                                                                                                                        |
| Study Duration        | 1-2 years                                                                                                                                                                                                                                                                                                                                                                                                                                                                                                                                                                                                                                                                                                                                                                                                                                                                                                                                                                                                                                                                                                                                                                                                                                                                                                                                                                                                                                                                                                                                                                                                                                                                                                                                                                                                                                                           |
| Study Intervention    | Subjects will be randomized (1:1) to receive superficial parasternal intercostal plane block with ropivacaine via ultrasound-guided catheter placement or sham block with saline. Catheters will be inserted into the superficial parasternal intercostal plane bilaterally under ultrasound guidance after skin closure. Following initial bolus dosing at the time of catheter placement, a continuous infusion with intermittent boluses every 3-4 hours of 0.2% ropivacaine, or equivalent volume of 0.9% normal saline, will be delivered via catheters for 48 hours post-catheter insertion.                                                                                                                                                                                                                                                                                                                                                                                                                                                                                                                                                                                                                                                                                                                                                                                                                                                                                                                                                                                                                                                                                                                                                                                                                                                                  |
| Duration of Treatment | Treatment will be delivered for 48 hours post-catheter insertion.                                                                                                                                                                                                                                                                                                                                                                                                                                                                                                                                                                                                                                                                                                                                                                                                                                                                                                                                                                                                                                                                                                                                                                                                                                                                                                                                                                                                                                                                                                                                                                                                                                                                                                                                                                                                   |
| Outcomes              | 
 
• Primary outcome: Cumulative postoperative opioid use measured as Milligram Morphine Equivalent (MME) up to 72 hours following catheter insertion
 
• Secondary outcomes: 
 
○ Median pain score as measured by a standardized numeric rating scale over 72 hours following catheter insertion (measured at rest and with coughing q12hours <math>\pm</math> 2 hours post-catheter insertion)
 
○ Cumulative postoperative opioid use measured as Milligram Morphine Equivalent (MME) from catheter insertion until discharge from hospital
 
○ Delirium assessed BID for 72 hours following catheter insertion
 
○ Quality of Recovery-15 Scale administered 24-96 hours post-surgery.
 
 
 
• Tertiary (exploratory) outcomes: 
 
○ Time from catheter insertion to extubation
 
○ Time from catheter insertion to first opioid analgesic provision following extubation
 
○ Time from catheter insertion to mobilization
 
○ ICU and hospital LOS
 
○ Postoperative nausea and vomiting, measured via a 10-point visual analogue scale BID and antiemetic medication requirements up to 72 hours following catheter insertion
 
○ Opioid requirements post-discharge as assessed by prescriptions provided at time of discharge and during post-discharge follow-up visit using both patient health record and direct patient recounting
 
○ Chronic post sternotomy pain/disability and patient reported outcomes assessed at 3 months <math>\pm</math> 4 weeks from surgery with McGill Pain Questionnaire as well as at 6 weeks <math>\pm</math> 2 weeks and 3 months <math>\pm</math> 4 weeks with the change in PROMIS 29 score
 
 
 
 |
| Statistical Analysis  | Categorical data will be summarized by frequencies and percentages, and continuous variables by means and standard deviations (or medians and interquartile ranges for non-linear data). For the primary analysis, we will perform linear regression, adjusted for sex and intraoperative opioid MME to assess the comparison between trial groups. A modified intention-to-treat analysis will be employed, including only patients who received the block, and excluding patients with prolonged intubation. Sensitivity analyses using complete intention-to-treat and per protocol populations will also be conducted.                                                                                                                                                                                                                                                                                                                                                                                                                                                                                                                                                                                                                                                                                                                                                                                                                                                                                                                                                                                                                                                                                                                                                                                                                                          |

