### 3.4 Tertiary (exploratory) Endpoints

- Time from catheter insertion to extubation
- Time from catheter insertion to first opioid analgesic provision following extubation
- Time from catheter insertion to mobilization
- ICU and hospital LOS
- Postoperative nausea and vomiting, measured via a 10-point visual analogue scale BID and antiemetic medication requirements up to 72 hours following catheter insertion
- Opioid requirements post-discharge as assessed by prescriptions provided at time of discharge and during post-discharge follow-up visit using both patient health record and direct patient recounting
- Chronic post sternotomy pain/disability and patient reported outcomes assessed at 3 months  $\pm$  4 weeks from surgery with McGill Pain Questionnaire as well as at 6 weeks  $\pm$  2 weeks and 3 months  $\pm$  4 weeks with the change in PROMIS 29 score (Attempts to obtain the 3-month data can continue for up to 6 months post-surgery before it will be considered a protocol deviation or the participant deemed lost-to-follow-up)

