### 5.2 Study Visits

#### *Visit S: Screening*

- Written informed consent
- Determination of eligibility
- Demographics, medical history, baseline medications including doses
- Physical examination, height and weight assessment, BMI
- Vital signs
- Laboratory assessments: CBC, creatinine/eGFR, electrolytes, coagulation testing
- Preoperative PROMIS 29 Score

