The analysis of covariance (ANCOVA) model with a fixed effects for treatment group, sex, BMI and intraoperative MMEs ( $<$ median,  $\geq$ median) will be used to analyze the primary efficacy endpoint. The least squares (LS) mean, standard errors, and 2-sided 95% confidence intervals (CIs) for each treatment group and for the mean difference compared to placebo will be estimated. The model will be fit assuming unequal variances for each treatment group. If substantial deviations from the model assumptions are observed, then supportive analyses, such as robust regression, non-parametric analyses, etc. will be considered. Missing values of predictors will either be imputed by the overall mean or most frequent category.

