### 3.4.2 Secondary Efficacy Endpoints

Pain score during the 72 hours following catheter insertion will be analyzed by a mixed model for repeated measures (MMRM), with random effects for intercept and time, fixed effects for treatment, sex, and intraoperative MMEs (<median, ≥median), and an unstructured covariance matrix.

The analysis of cumulative postoperative opioid use measured as MMEs from catheter insertion until discharge from hospital will be by the same methods as for the primary efficacy endpoint, including the joint model sensitivity analysis.

The analysis of incidence of delirium during the 72 hours following catheter insertion will be by logistic regression with fixed effects for treatment group, sex, and intraoperative MME (<median, ≥median). The treatment odds ratio (OR) and associated 95% confidence interval will be provided.

The analysis of Quality of Recovery-15 Scale administered 24-96 hours post-surgery will be by the same methods as for the primary efficacy endpoint.

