### 3.4.3 Exploratory Efficacy Endpoints

The analyses of time-to-event exploratory efficacy endpoints will be by proportional hazards models with fixed effects for treatment, sex, and intraoperative MMEs (<median, ≥median). The treatment hazard ratio (HR) and associated 95% CI will be provided. A cause-specific approach for competing terminal events (i.e., deaths) will be applied by censoring participants at the time of death. Cumulative incidences by treatment group will be estimated by Kaplan-Meier methods.

The analyses of incidence of postoperative nausea or vomiting will be by the same methods as pain score or delirium.

Opioid requirements post-discharge will be summarized by descriptive statistics.

The analyses of chronic post sternotomy pain/disability and patient reported outcomes assessed with the McGill Pain Questionnaire (3 months) and PROMIS 29 score (6 weeks, 3 months) will be by the same methods as for the primary efficacy endpoint.

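### The QoR-15 and McGill models contain no preoperative patient-reported measure although PROMIS-29 is collected at screening, so both comparisons may be less precise than the data allow

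*Combined protocol and SAP*

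**What the plan says.** **Timing of the instruments.** The protocol synopsis and protocol 3.3 give the recovery endpoint as "Quality of Recovery-15 Scale administered 24-96 hours post-surgery". Protocol 3.4 places the McGill questionnaire at the 3-month contact: "Chronic post sternotomy pain/disability and patient reported outcomes assessed at 3 months". Neither instrument appears at the screening visit. The only patient-reported instrument listed there (protocol 5.2, Visit S) is "Preoperative PROMIS 29 Score", which SAP 3.3.3 includes among the baseline characteristics to be tabulated by group.

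**Models.** SAP 3.4.2 states: "The analysis of Quality of Recovery-15 Scale administered 24-96 hours post-surgery will be by the same methods as for the primary efficacy endpoint". SAP 3.4.3 does the same for the later outcomes: "McGill Pain Questionnaire (3 months) and PROMIS 29 score (6 weeks, 3 months) will be by the same methods as for the primary efficacy endpoint". The method referred to is the ANCOVA of SAP 3.4.1, a "model with a fixed effects for treatment group, sex, BMI and intraoperative MMEs", with intraoperative MME split at its median and variances allowed to differ between groups. Baseline PROMIS-29 is named as a covariate in no model. SAP 3.4.1 also says that a missing predictor is filled in with the overall mean or the commonest category.

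**The concern.** The covariates were chosen for opioid consumption and then carried over to two patient-reported outcomes. None of them measures pain, function or wellbeing before surgery. Because neither QoR-15 nor McGill has a preoperative value of its own, the nearest available substitute is the screening PROMIS-29.

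If preoperative PROMIS-29 predicts these outcomes, leaving it out keeps that between-patient variation in the residual and widens the confidence intervals. The endpoints concerned are the secondary recovery scale and the exploratory chronic-pain questionnaire. What is at stake is precision on these two comparisons, obtainable from data the trial already collects.

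**Working it through.** **1. The plan's own figure.** SAP 2.2.2 gives a difference of 10 MME, SD 25, two-sided 5% and 90% power, with 133 per group. The normal approximation gives n = 2 × (1.960 + 1.282)² × (25/10)² ≈ 131.4, so 132 per group. With the noncentral t distribution, power is 0.8993 at 132 and 0.9015 at 133, so 133 is reproduced. This calculation covers the opioid endpoint only. The documents give no SD, effect size, power target or correlation for QoR-15 or McGill. I use 2 × 133 = 266 analysed patients only as a reference size.

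**2. Formula.** Let r be the correlation of preoperative PROMIS-29 with the outcome, given treatment, sex, BMI and intraoperative MME. Adding it as a linear covariate multiplies the variance of the treatment difference by 1 − r² and the standard error by √(1 − r²). The equivalent number of patients is 266/(1 − r²). This assumes a linear relation, the same r in both groups and complete baselines.

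**3. Cost of the extra term.** The present mean model has five coefficients (intercept, treatment, sex, BMI, MME). The cost of one more is approximately (266 − 6)/(266 − 7) = 260/259 = 1.0039, about 0.4% of variance. Break-even is at 1 − r² = 259/260, that is r = √(1/260) ≈ 0.06.

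**4. Results.** Every r is an assumption.

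| r | Variance factor | Factor including the 0.4% cost | Fall in standard error (before cost) | Equivalent patients (before cost) |
|---|---|---|---|---|
| 0 | 1.00 | 1.004 | 0.0% | 266 |
| 0.1 | 0.99 | 0.994 | 0.5% | 269 |
| 0.2 | 0.96 | 0.964 | 2.0% | 277 |
| 0.3 | 0.91 | 0.914 | 4.6% | 292 |
| 0.4 | 0.84 | 0.843 | 8.3% | 317 |
| 0.5 | 0.75 | 0.753 | 13.4% | 355 |

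**5. Check by simulation.** In 4000 simulated trials per value of r, with 133 per group, the ratio of standard errors with and without the covariate was 1.002 at r = 0, 0.951 at 0.3 and 0.862 at 0.5. Theory gives 1.000, 0.954 and 0.866.

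**6. In terms of power, for illustration.** For an assumed standardised effect of 0.40 (the primary endpoint's 10/25, borrowed), power goes from 90.4% to 91.5% at r = 0.2, 92.8% at 0.3 and 96.5% at 0.5. For an assumed effect of 0.25 it goes from 53.1% to 54.8%, 57.0% and 65.3%.

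**The case against.** The strongest reply is that the plan contains no error here. Both models are stated clearly, and any covariate list could be lengthened. The documents also give reasons to expect a low r. Protocol 4.2 excludes chronic opioid use and chronic pain disorders, which may narrow the preoperative spread. QoR-15 is taken one to four days after sternotomy, when the operation and its complications may dominate. Protocol section 2 puts chronic pain at no more than 35% at 3 months, so many McGill scores may lie near the floor. PROMIS-29 is also a different instrument from either outcome, and filling in missing baselines by the mean dilutes any gain.

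Most of this stands as a limit on size, and it is why the range must start at r = 0. It does not remove the point. The term costs about 0.4% of variance, cannot bias a randomised comparison and needs no new data. The SAP has itself already added BMI to the protocol's covariates of sex and intraoperative MME (protocol section 7).

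A reader might infer three stronger things, and the documents support none of them:

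- **That the planned comparisons are biased, or that a chance preoperative imbalance invalidates them.** Randomisation keeps them valid, the confidence interval already covers chance imbalance, and SAP 3.3.3 would make an imbalance in PROMIS-29 visible.
- **That a known, sizeable amount of precision is being lost.** No correlation is given from which to size it.
- **That the trial needed preoperative QoR-15 and McGill assessments.** Nothing in the plan depends on them.

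The lack of a baseline term in the model for PROMIS-29 as an outcome is a separate matter.

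**Conclusion.** The point holds as a possible loss of precision on one secondary and one exploratory endpoint. The two models leave out the only preoperative patient-reported measure that the trial collects. Whether this matters depends on r: the loss is negligible below about 0.1, small at 0.2, and worth having from about 0.3 to 0.4 upwards. No stated power is lost, because the documents set no power target for either endpoint. It is a desirable refinement, not a necessary correction.

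**What to change.** In SAP 3.4.2 (QoR-15) and 3.4.3 (McGill), add one named preoperative PROMIS-29 score to the ANCOVA as a continuous covariate. It should be the same score that the SAP analyses as the PROMIS-29 outcome. The documents do not say which score or domain that is, so the SAP must name it; otherwise the choice is left to the analyst. Missing baselines can follow the predictor-imputation rule in SAP 3.4.1, so no patient is dropped for lack of one.

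The change should be made before unblinding. SAP section 1 says the plan is finalised before database lock, and protocol 3.7 keeps the blind until lock. If the data are already unblinded, keep the planned models and report the adjusted ones as labelled supportive analyses.

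The cost is a short SAP amendment, a decision on the score and one degree of freedom in each model. No new data are needed.
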